### Objectives and Hypotheses

The primary objective of this study is to describe the feasibility and acceptability of flexible, modular, and hybrid IACP for adolescents with EDs. Secondary aims include describing the baseline characteristics of the adolescents who enroll in the IACP, describing the preliminary effectiveness of the IACP for adolescents with EDs in an uncontrolled naturalistic setting, and describing the moderating role of age, ED diagnosis (eg, anorexia nervosa vs other ED diagnoses), length of illness, and level of attendance on clinical response to the IACP.

We hypothesize that recruiting and retaining participants in the IACP would be feasible and acceptable. We expect that participants will mostly present restrictive ED symptomatology, which is representative of the patient population seen in the ED clinic where the study will be conducted; participants will present comorbid symptomatology and ED-related behaviors, such as anxiety and depressive symptoms [31,32], high levels of affective reactivity [33] and perfectionism scores [34], poor coping [35] and self-esteem [36] skills, and high levels of social media use [37], as reported in the literature. We expect that participation in the IACP will be associated with a reduction in ED psychopathology, from baseline to the end of treatment, and that patient age, ED diagnosis, length of illness, family connectedness, and the number of hours of therapy attended will act as moderators of the preliminary effectiveness of the intervention. Although there is no consensus on moderators of treatment outcomes in the adolescent population, these moderators were chosen based on limited evidence from several reviews [8,38,39] that have identified individual, clinical, and family-related factors that are related to treatment response.

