## Methods

### Overview

Our team will conduct a naturalistic study of the IACP for youth with EDs that will gather 3 types of data. First, the feasibility of the IACP will be evaluated using recruitment, retention, and adhesion-to-protocol rates. Second, the acceptability of the IACP program and web-based delivery method among youth participants will be measured using youth and parent satisfaction questionnaires. Finally, the preliminary effectiveness of the IACP will be described using quantitative self-report questionnaires pertaining to ED symptomatology, and several moderators of this effect will be investigated. Body mass index (BMI) and quantitative self-report measures of comorbid psychopathology will be used as secondary outcome measures to describe the preliminary effectiveness of the intervention in an uncontrolled naturalistic setting.

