### Population

Individuals eligible for the study will be between 12 and 18 years of age, have a diagnosed ED according to the DSM-5 (Diagnostic and Statistical Manual of Mental Disorders, Fifth Edition) criteria [40], and will already have received medical treatment in the hospital or ambulatory setting at our specialized ED clinic. This clinic is located in a tertiary pediatric hospital in a large city in the province of Quebec, which serves both a multicultural urban population representative of other large cities in North America in addition to the surrounding suburban and rural populations. Individuals who meet these criteria will be invited to participate in the IACP and the current research. To be eligible for the IACP, individuals must be available to participate in all aspects of the proposed intervention (including pre- and postintervention measures, individual, family, and group sessions, and an intake and feedback meeting with the IACP clinical team).

Individuals will be excluded from the IACP (and the current research study) if they require hospitalization for medical stabilization when evaluated for recruitment. In addition, the intervention will be discontinued and the individual referred to the appropriate service if they become medically unstable during the program (eg, heart rate <45 bpm, body temperature <35.5 °C) or express acute psychiatric distress (eg, active suicidal ideation requiring hospitalization).

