### Recruitment, Enrollment, and Consent

Clinicians working in ambulatory and hospital settings at our specialized ED clinic will refer patients who are suitable for the IACP. These patients will be screened for eligibility by an IACP clinical coordinator. All patients who meet the criteria for participation in the IACP will receive a brief explanation of the study during the initial screening meeting with the clinical coordinator and will be presented with the opportunity to meet a research assistant to discuss consent if they are interested in participating in the research study. It will be made clear that participation in the research study is optional and that it will not affect any care or services received in the IACP.

The meeting with the research assistant will take place with the eligible participant and at least one parent, either in-person or via the secure Teams videoconferencing platform. The research assistant will verbally explain the objectives of the study, the main procedures involved, and the potential benefits and risks of participation. The participant and their parents will be given time to ask questions and consider participating. If they agree, a consent form (summarizing the verbal explanation of the study) will be presented to them for both parents and participants to sign.

Recruitment will occur on an ongoing basis over the 2-year study period. We expect that approximately 100 patients will be recruited (see the section on power calculation below for more details).

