### Attrition and Compliance

We expect to recruit approximately 80% (100/120) of eligible participants—that is, 80% of all youth enrolled in the IACP—to our study, which is a conservative estimate based on previous literature [41]. Participation in the research study entails no additional commitment from eligible participants, given that all study materials are also an integral part of the IACP. Further, we expect attrition to be less than or equal to 25% (25/100), based on the current literature, which suggests a 7% to 42% dropout rate for adolescents enrolled in day treatment programs for the treatment of EDs [17,42-45], and also considering the flexible, modular, and hybrid nature of our program, which may allow us to improve retention rates.

Participants who attend at least one session per week of treatment in the IACP (and complete both pre- and postintervention materials) will be considered sufficiently exposed to the intervention and, thus, will be included in the data analysis on the preliminary effectiveness of the program.

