### Data Collection

Data will be collected at baseline (clinical and demographic information and preintervention self-report questionnaires), weekly (youth and parent satisfaction questionnaires), and immediately after the end of treatment (postintervention self-report and satisfaction questionnaires), as outlined in Figure 1. The clinical program coordinator will be responsible for collecting all data, deidentifying the data, and sending all deidentified data (including only participants’ random study ID) to the research team. Data to be collected include demographic and clinical information at baseline, growth curve charts, BMI pre- and postintervention, self-report standardized outcome questionnaires, acceptability (satisfaction) surveys, and measures of feasibility. All self-report questionnaires and surveys will be completed either on paper (if participants are present on site) or web-based (on a laptop or smartphone) using password-protected interactive PDF format questionnaires that will be sent to the participants using a secure email address.

Demographic and clinical information at baseline, including age, sex, level of education, diagnosis, presenting ED symptoms, duration of illness, ED treatment history (including past hospitalizations), maximum and minimum weight, comorbid symptomatology, and past medical history, will be collected by the clinical program coordinator during the intake visit for the IACP.

BMI will be calculated at baseline and at the end of treatment. Weight (with clothing on but without coats, shoes, boots, or cold weather accessories) and height (without shoes) will be measured during the first and last appointments with the clinical team using an electronic scale and a standard wall measuring scale. BMI will be calculated by dividing body weight in kilograms by the square of the height in meters.

Feasibility data will be collected by the IACP clinical staff throughout the duration of the study and will include recruitment and retention rates, in addition to measures of adherence to the protocol (Table 1).

**Table 1 table1:** Summary of feasibility measures.

Outcome	Target
Recruitment rate	80% (100/120) of eligible participants (ie, of all adolescents participating in the IACP^a^) will enroll in the study and complete the baseline measure.
Retention rate	≤25% (25/100) of enrolled participants lost to follow-up.

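### The recruitment rate in Table 1 is a study-consent rate among adolescents already in the IACP, so it does not test the hypothesis that recruiting into the IACP is feasible

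*Protocol article*

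**What the plan says.** Four parts of the protocol article bear on this point.

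- **Objective and hypothesis.** The article sets its aim as follows: "The primary objective of this study is to describe the feasibility and acceptability of flexible, modular, and hybrid IACP for adolescents with EDs" (section Objectives and Hypotheses). The matching hypothesis concerns entry to the programme as well as staying in it: "We hypothesize that recruiting and retaining participants in the IACP would be feasible and acceptable".
- **Measures (Methods, Overview).** "the feasibility of the IACP will be evaluated using recruitment, retention, and adhesion-to-protocol rates".
- **Definition (Data Collection, Table 1).** The target is 80%, given as 100 of 120, of a group glossed as "ie, of all adolescents participating in the IACP". The numerator is those who enrol in the study and complete the baseline measure. Attrition and Compliance gives the same denominator in prose, as youth enrolled in the IACP.
- **Route to the denominator.** Clinicians refer patients they think suitable. Then "These patients will be screened for eligibility by an IACP clinical coordinator" (Recruitment, Enrollment, and Consent). The Population section requires age 12 to 18, a DSM-5 diagnosis, earlier treatment at the clinic and no need for hospitalization for medical stabilization, and adds that "individuals must be available to participate in all aspects of the proposed intervention". Consent to the study is a separate and optional step that does not alter care. Taking part in the study "entails no additional commitment from eligible participants, given that all study materials are also an integral part of the IACP" (Attrition and Compliance).

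**The concern.** The hypothesis is about bringing adolescents into a hybrid programme. The rate offered in support starts counting only once they are in it. Patients who are referred and meet the clinical criteria but decline the IACP, or who cannot commit to all its components, fall before the denominator, and no row of Table 1 counts them. What the rate then captures is whether families already in the programme agree to research use of questionnaires they complete anyway.

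Meeting the 80% target would therefore say little about whether eligible families accept this form of care. That matters because the Discussion (Future Implications) presents the programme as a way of removing barriers such as distance and disruption to school and family life. Families for whom those barriers remain are the ones who might not enter.

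**Working it through.** **Inputs.** From Table 1 and Attrition and Compliance: 120 adolescents in the IACP, 100 of them enrolled in the study with a baseline measure, target 80%. Not in the article: the number of eligible patients referred, and hence programme uptake. Uptake is written u below and varied as an assumption.

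**The plan's own figure.** 100/120 = 83.3%. The stated 80% would need 0.80 × 120 = 96 enrolled, or 100/0.80 = 125 in the IACP. The Abstract and the Attrition section say approximately 80%, so this is loose rounding, and nothing below depends on it.

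**What the rate depends on.** Let E be the number of eligible referred patients and u the share who start the IACP.

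- IACP starters = u × E = 120, so E = 120/u.
- Table 1 rate = 100/120 = 83.3%. Neither u nor E appears in it.
- Enrolled among eligible = 100/E = u × 83.3%.

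| Assumed uptake u | E = 120/u | Table 1 rate | Enrolled/eligible = 100/E |
|---|---|---|---|
| 100% | 120 | 83.3% | 83.3% |
| 80% | 150 | 83.3% | 66.7% |
| 60% | 200 | 83.3% | 50.0% |
| 50% | 240 | 83.3% | 41.7% |
| 30% | 400 | 83.3% | 25.0% |

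The third column does not move. That follows from the definition, not from the values chosen for u.

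**Is the numerator more than consent?** It also requires the baseline measure. Those questionnaires are part of IACP care for everyone in the programme, so the requirement adds little beyond agreement to take part in the research.

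**Is the denominator a slip in the table?** No. Table 1 and Attrition and Compliance agree on it. The Population section is less tidy: it speaks of inviting those who meet the criteria to both the IACP and the study, which is a wider group than those participating in the IACP. The word eligible is thus used in two senses.

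**The case against.** The strongest reply is that the definition is open. Table 1 states its denominator, and both it and the Attrition section speak of enrolment in the study, so a careful reader is not misled about what is counted. Referral and screening counts are also commonly left to a full protocol, screening log or flow diagram, and their absence from an article does not show that they will go unreported. Both statements are fair. They do not remove the mismatch, because the article itself names this rate as a measure of IACP feasibility and hypothesizes feasibility of recruiting into the IACP. The criticism is of a stated definition, not of an omitted detail.

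Three stronger readings are tempting, and the document does not support them.

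- *Uptake is the primary question, so the primary objective goes unanswered.* A reader might infer this, but the objective covers feasibility and acceptability as a whole. Loss to follow-up, weekly session attendance, questionnaire completion and satisfaction do describe the programme after entry. Uptake is one component.
- *A high consent rate alone would let the programme be called feasible and exported to other sites.* Table 1 also sets a retention target and three adherence targets, and the analysis of feasibility is descriptive. Future Implications requires the programme to be feasible, acceptable and preliminarily effective, and the reasons it gives for transfer are standardized questionnaires and planned guidelines.
- *The availability criterion inflates retention and adherence.* It may favour likely attenders, but the article does not say how many patients it excludes. This is a possibility to keep in mind when interpreting those rates, not an established bias. Requiring availability is in itself an ordinary entry condition.

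**Conclusion.** The point holds in a limited form. The Table 1 recruitment rate is essentially a study-consent rate. It does not test the protocol's own hypothesis on recruiting into the IACP, which is one component of the primary objective.

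At the planned counts the rate is 83.3% at any level of programme uptake. Enrolment among eligible patients could be 25.0% or 83.3% behind that same figure if uptake were 30% or 100%. Those percentages only illustrate the insensitivity: the article gives no uptake, and nothing in it shows that uptake will be low. The conclusion rests on the stated numerator and denominator, and on the article's statements that joining the study adds no commitment and leaves care unchanged. It should be corrected before results are reported, but it does not undermine the other feasibility and acceptability measures.

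**What to change.** 1. Relabel the present row of Table 1 as the study consent rate, keeping its numerator and denominator, and do not present it as evidence of recruitment into the programme.
2. Add a programme-uptake row. Numerator: adolescents who start the IACP, whether or not they consent to the study. Denominator: referred adolescents who meet the Population section's criteria on age, DSM-5 diagnosis, earlier treatment at the clinic and no need for hospitalization.
3. Report declined and not available for all components separately, as reasons for non-entry. Counting unavailability as non-entry is a choice of definition, and showing the two groups apart lets a reader recompute uptake either way.
4. State that the denominator is limited to patients whom clinicians chose to refer, so even this rate does not describe all patients of the clinic. Note also that the availability criterion may favour likely attenders when retention and adherence are interpreted.
5. Use the word eligible in one sense in the Population section, the Attrition section and Table 1.

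The eligibility rules do not change. The counts come from screening the coordinator already does and can be given in aggregate, so the cost is one table row and a tally of reasons. The downside is that the headline figure may look less favourable.

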Adherence to protocol	At least 70% (70/100) of participants complete at least one therapeutic session per week of treatment in the IACP. At least 70% (70/100) of participants complete all pre- and postintervention questionnaires. At least 70% (70/100) of participants complete at least one therapeutic session per week and all pre- and postintervention questionnaires.

^a^IACP: Intensive Ambulatory Care Program.

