### Intervention

The intervention uses a family-centered, educational, and motivational approach that is based on the biopsychosocial model of EDs as described in Aimé and Bégin [46]. This model theorizes that a combination of sociocultural, environmental, familial, and individual factors, in addition to biological predispositions, converge to contribute to both the development and maintenance of disturbed beliefs and behaviors that characterize EDs. The therapeutic and psychoeducational modules (Table 2) were created based on this theory [46] and on a variety of similar sources such as books by Daniel J Siegel on mindfulness and by Martha M Linehan on impulse control [47], on cognitive behavioral and psychoeducational activities that are carried out in numerous ED treatments (eg, an open letter to my anorexia, metaphors for change, etc), and on original material created in partnership with patients.

Each participant will have an individualized treatment plan combining one or more modules, which will be established based on the initial questionnaire evaluation results and discussions between the clinician, the participant, and their family. Modules on one or more of the following themes will be presented as follows: (1) EDs and related psychopathology; (2) mental health and emotional regulation; (3) stress and anxiety management; and (4) identity, relationships, and life cycle issues in adolescence. Parents will be invited to participate in interventions pertaining to the physical and psychological components of EDs, meal accompaniment, stress, anxiety, hyperactivity management, and family life.

The intake and evaluation process, which will guide the creation of an individual treatment plan, will take place over 1 week. Following this, the intervention will take place over 4 weeks, with the possibility of extending it by 2 weeks, based on a discussion with the clinical team and the participant’s individual needs and progress. The intervention will conclude with 1 week of feedback and evaluation. Overall, the programming will last for 6 to 8 weeks.

**Table 2 table2:** Overview of the 4 therapeutic modules and corresponding activities and interventions offered within the Intensive Ambulatory Care Program.

Module	Activities and interventions
EDs^a^ and related psychopathology	Virtual meal accompaniment Hyperactivity management ED recovery and sources of motivation Perfectionism Body image

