Mental health and emotion regulation	Recognizing emotions Emotion regulation Impulsivity and anger Suicidal and parasuicidal behaviors
Stress and anxiety management	Recognizing emotions Mindfulness Relaxation techniques Psychoeducation about stress
Identity, relationships, and lifecycle issues in adolescence	Changes during adolescence and fear of growing up Self-esteem and self-affirmation The influence of social media Relationships with parents and friends Communication

^a^ED: eating disorder.

The time commitment for program participants will be variable but will involve a minimum of two to three 60- to 90-minute sessions per week, including meal accompaniment and preparatory activities with the adolescent and at least one parent or guardian. This represents a total of approximately 3 to 4 hours of programing per week. This will be in addition to regular planned outpatient clinical appointments with doctors, psychologists, social workers, etc. which will be considered usual care and which are not part of the IACP.

The modules of the intervention will be delivered using various formats, including in-person and web-based individual meetings, in-person and web-based meetings with parents, web-based synchronous therapy activities (eg, relaxation or mindfulness) administered by clinicians, individual web-based asynchronous therapy activities completed alone by participants with web-based feedback provided by clinicians, web-based viewing of prerecorded informational videos, and participant and family completion of personal logbooks and assignments. Each module has a set format (eg, individual vs group; in-person vs web-based) and was developed by the clinical team based on clinical experience and relevant literature.

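### The adherence target is set at one session per week, below the programme's own stated minimum of two to three, so meeting it would not by itself show feasibility at the defined intensity

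*Protocol article*

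**What the plan says.** The primary objective is to describe feasibility and acceptability. Feasibility has three measures: recruitment, retention and adherence to protocol. Table 1 (Data Collection) gives the adherence row three targets of 70% each. The first is "At least 70% (70/100) of participants complete at least one therapeutic session per week of treatment in the IACP". The second concerns completion of questionnaires. The third combines the two: "At least 70% (70/100) of participants complete at least one therapeutic session per week and all pre- and postintervention questionnaires". The Results paragraph of the Abstract repeats the combined target.

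The Intervention section describes what taking part involves. It says that the time commitment varies, but that it "will involve a minimum of two to three 60- to 90-minute sessions per week", and adds: "This represents a total of approximately 3 to 4 hours of programing per week". On duration, "the intervention will take place over 4 weeks, with the possibility of extending it by 2 weeks". The Population section makes availability a condition of entry: "individuals must be available to participate in all aspects of the proposed intervention".

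Attrition and Compliance uses the one-session threshold for a second purpose. "Participants who attend at least one session per week of treatment in the IACP", and who also complete the questionnaires before and after treatment, "will be considered sufficiently exposed to the intervention and, thus, will be included in the data analysis on the preliminary effectiveness of the program".

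**The concern.** The programme has a stated weekly floor, and the measure called adherence to protocol is set below it. No section says why attendance below the floor counts as adherence, and no measure in Table 1 compares sessions attended with sessions planned.

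Intensity is part of what is being tested. The programme is named as intensive, and the Introduction places day treatment between hospitalization and ambulatory care. A feasibility measure that passes at well under the minimum dose says that participants stayed in touch with the programme. It does not say that the programme could be delivered and attended as described. The Future Implications section ties use at other sites partly to a positive feasibility result, so what that result means matters.

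**Working it through.** **Inputs**

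- Adherence threshold: 1 therapeutic session per week (Table 1).
- Target: 70 of 100 participants (Table 1).
- Programme minimum: 2 to 3 sessions per week (Intervention).
- Duration: 4 weeks, or 6 if extended (Intervention).

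**The plan's own figure.** 70/100 = 70%, as stated.

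**Share of the minimum attended at the threshold** = threshold sessions / minimum sessions.

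| Period | Sessions at the threshold | Programme minimum | Share |
|---|---|---|---|
| One week | 1 | 2 to 3 | 1/2 = 50% to 1/3 = 33% |
| 4 weeks | 4 × 1 = 4 | 4 × 2 = 8 to 4 × 3 = 12 | 4/8 = 50% to 4/12 = 33% |
| 6 weeks | 6 × 1 = 6 | 6 × 2 = 12 to 6 × 3 = 18 | 6/12 = 50% to 6/18 = 33% |

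Two to three is a minimum, so anyone whose plan holds more than three sessions per week would be below 33% of their own plan at the threshold.

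**What the target permits.** The first adherence target is met if 70 participants each attend one session per week. In that limiting case the number who reached the programme minimum is 0. The combined target adds questionnaires but no further attendance, so it permits the same. This shows what the criterion allows and is not a forecast.

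**Do the two places count the same thing?** The Intervention section includes meal accompaniment within its two to three sessions. If Table 1 meant something narrower by a therapeutic session, the ratio would not apply. The article draws no such line: Table 2 lists meal accompaniment among the module activities, and Outcome Measures counts it among the therapeutic activities that participants rate for satisfaction.

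**Effect on the effectiveness set if the threshold were raised there too.** The rule in Attrition and Compliance matches the combined target, so a trial that just meets that target has 70 participants in the effectiveness set. Power Calculations gives 68 as the number required, before moderators and dropout are added. The margin is 70 − 68 = 2, and a stricter rule could soon use it up.

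**The case against.** The strongest reply is that nothing here is contradictory. The Intervention section describes what is scheduled and says that it varies. Table 1 sets the lowest attendance that counts. An exposure threshold below the scheduled dose is ordinary in a flexible pilot, this one is stated consistently in three places, and the feasibility analysis is descriptive. This largely stands. A reader might infer that the sections flatly contradict each other, but they describe different quantities. What remains is the label and the missing rationale: the variation in the Intervention section operates above a stated minimum, and adherence to protocol is measured below it.

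A second reply is that dose is analysed anyway. Hours of therapy attended is a hypothesised moderator, level of attendance is to be studied as a moderator, and sessions attended may enter as a covariate. That is true, but these analyses concern change in symptoms. They leave the feasibility measure as it is.

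Three stronger readings are tempting, and the documents do not support them:

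- **That the shortfall reaches 25% when measured in hours.** This divides the shortest session (1 h) by the largest weekly total (4 h). Four hours of 60-minute sessions is four sessions, outside the stated two to three. With sessions of equal length the lowest share is 33%. The weekly hours may also include asynchronous activities, videos and logbooks, and the article does not say which of these count as sessions.
- **That participants will in fact cluster at one session per week.** Nothing in the article suggests this.
- **That the rule is also too strict, because one missed week fails a full attender.** The article does not say how a missed week is scored, and such detail is commonly left to the full protocol or analysis plan.

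**Conclusion.** The point holds as a weakness in how one primary feasibility measure is defined and labelled. At the threshold a participant has attended 33% to 50% of the programme's own minimum (4 of 8 to 12 sessions over 4 weeks, or 6 of 12 to 18 over 6), so a result of 70% or more would not by itself show feasibility at the defined intensity. This rests on two assumptions: that a session means the same in Table 1 and in the Intervention section, and that the two-to-three range is a floor, as its wording says.

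The change is worth making because it is cheap and bears on the primary objective. The point takes no view on how intensive treatment should be. Nor does it show that the effectiveness analysis set is wrongly defined, although a reader might infer this because the same threshold is used there. That is a separate matter.

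**What to change.** Reconcile the Results paragraph of the Abstract, Attrition and Compliance, the adherence row of Table 1, and the Intervention section, as follows:

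1. Report, for each participant, sessions attended divided by sessions scheduled in the individual plan.
2. Report the proportion of participants who reach the programme's stated weekly minimum. The sponsor must say which value of the two-to-three range applies, since a range gives no cut-off.
3. Read the 70% adherence target against the proportion in item 2.
4. Keep the one-session-per-week figure, relabelled as a minimum-engagement level and not as adherence to protocol.
5. Leave the entry rule for the effectiveness analysis in Attrition and Compliance unchanged, and add a sentence giving its rationale. Tightening it here would shrink that set.

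Cost: some rewording in those places, and a 70% target that is harder to meet. The protocol already plans to use attendance, but the article does not say that the number of sessions scheduled per plan reaches the research team. That item would have to be added to the deidentified data that the clinical coordinator sends.
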